#### Secondary outcomes

The secondary outcomes of the study will be changes in the rate of suicide deaths, and changes in suicidal acts (combined deaths and attempts) within each site at 24 months relative to the control baseline period. To assess changes in mortality rates, unit-level mortality data (i.e., individual suicide cases) geocoded to trial-site geographic boundaries or to NSW will be acquired from the National Coronial Information System (NCIS) for all registered suicide deaths in NSW in the period 2006–2021. The method for identifying cases and assigning them to sites is the same as for the primary outcome. To further examine the effects of secular trends on the primary and secondary outcomes, sensitivity analyses will examine whether changes in suicide attempts, acts and deaths were different in trial sites to the rest of NSW. This analysis will assist in controlling for broader social and economic influences on suicide rates.

#### Recruitment and consent

Following the EOI selection process, successful applicants were notified of their acceptance into the LifeSpan trial. To confirm their participation in the trial, a contract describing roles, responsibilities, and key performance indicators was prepared and signed by the Black Dog Institute and the lead agency for each site.

#### Follow-up

Primary and secondary outcome data will be acquired for 12 months post baseline (end of Year 1 of active intervention) and 24 months post baseline (end of Year 2 of active intervention), though the primary point of interest is the latter.

#### Data management

The LifeSpan data environment will be hosted on a stand-alone secure server maintained by the University of New South Wales. Access to this secure server is through unique staff identification accounts and passwords. The raw data within the environment is stored in project-specific folders related to ethical agreements for access. These folders are protected by an Active Directory Rights Management Service (ADRMS) and are only accessible by individuals listed on appropriate ethics agreements. The data team listed on these agreements transforms the raw data into SAS datasets, which are protected by both AD RMS and SAS metadata security permissions. Datasets are then made available to researchers granted access dependent on ethical approval.

#### Sample size and statistical analysis

In the primary outcome analysis, changes in suicide attempt presentation rates per 100,000 population will be tested by comparing the mean annual attempt rate from July 2012 until the implementation date (pre-implementation) with the mean annual attempt rate from the implementation date till the end of the active implementation period (24 months post baseline), combined across all four trial sites. To determine whether the changes in trial-site suicide attempt rates were different to those occurring elsewhere, sensitivity analyses will use the suicide attempt rate for the rest of the NSW population as a background rate. Subsequent analysis will examine changes in treated suicide attempt rates pre and post implementation by individual site. The treated suicide attempt rate will be calculated per 100,000 population using the three linked datasets described for the primary outcome: ambulance data, ED data, and admitted patient data.

To examine changes in suicide deaths, the pre- and post-baseline rates per 100,000 will be calculated using data from the National Coronial Information System. As for the suicide attempt rates, the suicide death rates will be examined for all four trial sites collectively and for each individual site and compared with the background suicide death rates for the remainder of the NSW population in sensitivity analysis.

The alpha level will be set at 0.05 for all analyses.

The mean rate of treated suicide attempt presentations in the period 2005–2013 was approximately 250 per 100,000 per year in the four target sites, based only on hospital admission records. We have previously calculated that the nine strategies could, cumulatively or synergistically, reduce the rate of attempts by up to 30% [6]. However, the magnitude of the effect of a multilevel approach is likely to vary by the extent and length of implementation, the reach of exposure of individuals to multiple strategies, and the existing quality and availability of services and initiatives within communities at baseline. Detecting such change within one trial site relative to another trial site, with 90% power, would require a population within each site of at least 79,000 people. As each trial site has at least 145,000 population, we will be able to detect reductions of approximately 7% in suicide attempt rates within each site.

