### Participants and eligibility criteria

LifeSpan aimed to deliver interventions which were integrated in a healthcare region. Regions were defined as being one or more Local Government Areas (LGAs) which interact meaningfully and fall within the boundaries of a single Local Health District or a Primary Health Network. Lead agencies within NSW were invited to submit a written application as part of an Expression of Interest (EOI) selection process. Lead agencies could be a Local Health District, Primary Health Network, or non-government organization, and needed to demonstrate that they had strong relationships with other key agencies within their region in order to deliver the programs within the LifeSpan model. Applications were assessed by a panel of five individuals holding senior leadership positions in the mental health and suicide prevention sectors, including a National Mental Health Commissioner, the Director of the Mental Health Australia Board, representatives from the NSW Ministry of Health and the NSW Mental Health Commission and NSW Aboriginal Mental Health Workforce Program.

The sites were rated against the following five key selection criteria designed to demonstrate feasibility to implement LifeSpan:
Capability and capacity of the lead agency and partnership consortiumProposed model, partnerships and project planRisk management processesCommunity engagement and communication planIndicative budget to support implementation

In addition to the above inclusion criteria, sites needed to be able to yield reliable outcome data on rates of suicide attempts and suicide deaths. Accordingly, sites were required to have a minimum base population of 145,000 persons to allow for sufficient statistical power to detect a primary intervention effect. Archival data on suicide mortality and non-fatal hospital admissions for intentional self-harm were analyzed in a preceding early phase scoping study [10] to allocate LGA geographies into quartiles for suicide mortality and morbidity indicators. LGAs with incidence rates that fell within the top quartile for suicide mortality and/or non-fatal incidents were prioritized for site selection in addition to the EOI inclusion criteria, to ensure that the LifeSpan intervention would be implemented in areas with greatest need for suicide prevention efforts. The following sites were selected as a result of this process (Table 1).

**Table 1 Tab1:** Trial sites selected to receive the LifeSpan intervention

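### The 7% reduction said to be detectable within each site does not follow from the stated inputs: one site of 145,000 supports about 13–14% (pre versus post) or 23% (site versus site), and 7% fits the four sites pooled

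*Protocol article*

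**What the plan says.** All in the protocol article. In the section on sample size and statistical analysis the baseline attempt rate "was approximately 250 per 100,000 per year in the four target sites, based only on hospital admission records", and the nine strategies together are credited with a reduction of at most 30%. The power statement follows. Its comparison is given as "Detecting such change within one trial site relative to another trial site". The size attached to it is stated so: this, "with 90% power, would require a population within each site of at least 79,000 people". The next sentence opens "As each trial site has at least 145,000 population" and concludes that "we will be able to detect reductions of approximately 7% in suicide attempt rates within each site". No formula, time base or sidedness is printed. The only error rate given is "The alpha level will be set at 0.05 for all analyses".

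The same section defines the primary analysis as a comparison of the mean annual rate from July 2012 to implementation with the mean annual rate over the following 24 months, all four sites together. Pre/post changes in individual sites come as a later analysis. In the section on participants and eligibility criteria, "sites were required to have a minimum base population of 145,000 persons to allow for sufficient statistical power" for the primary intervention effect.

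**The concern.** The two power sentences stand next to each other, and the second is presented as a consequence of the first. The population rises from 79,000 to 145,000, a factor of 1.84. A detectable difference shrinks roughly with the square root of the population, so 30% should fall to about 30% × √(79,000/145,000) = 22%. Going from 30% to 7% would need roughly (30/7)² ≈ 18 times the population on that simple scaling, not 1.84 times.

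This is the only detectable effect the protocol gives for the sites it actually has, and site-level analyses of attempts are planned. The section itself says that the effect will vary with implementation and treats 30% as a ceiling, so modest site effects are plausible. A reader who trusts the 7% would take a non-significant result in one site as good evidence against a modest benefit, when the chance of detecting it was far below 90%.

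**Working it through.** **Inputs from the sample size section.** Baseline p₁ = 0.0025 per person-year; reduction of 30%, so p₂ = 0.00175; alpha 0.05; power 90%; one site against another, taken as 1:1 with one year each; at least 145,000 people per site, so at least 580,000 in four. The post period is 2 years. The pre period runs from July 2012 to each site's start. Start dates are not in the text, so 4.5 to 5.5 years is assumed.

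**Step 1: reproduce the 79,000.**

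n = (1.960 + 1.282)² × [p₁(1−p₁) + p₂(1−p₂)] / (p₁ − p₂)²

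= 10.507 × (0.0024938 + 0.0017469) / 0.00075² = **79,215**.

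The pooled-variance form gives 79,219. Other error rates do not fit: one-sided 5% with 90% power gives 64,566, and two-sided 5% with 80% power gives 59,176. The 79,000 is therefore a two-sided 5%, 90% power figure.

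**Step 2: the same formula at 145,000 per site.** Solving for the reduction r that gives n = 145,000 yields r = 0.2265, about **23%**. Weaker error rates do not help enough: 19.7% at two-sided 80% power, 20.6% at one-sided 90% and 17.6% at one-sided 80%.

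**Step 3: population needed for 7%.** With p₂ = 0.002325:

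n = 10.507 × (0.0024938 + 0.0023196) / 0.000175² ≈ **1.65 million per site**, which is 11.4 times 145,000.

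**Step 4: read the claim as pre versus post.** With person-years T₁ before and T₂ after, r solves

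r × p₁ = 3.2415 × √[p₁(1−p₁)/T₁ + p₂(1−p₂)/T₂], where p₂ = p₁(1−r).

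For one site over 5 and 2 years, T₁ = 725,000 and T₂ = 290,000. The root is √(3.440×10⁻⁹ + 7.439×10⁻⁹) = 1.043×10⁻⁴, so r = 3.2415 × 1.043×10⁻⁴ / 0.0025 = 13.5%. With pooled variance it is 13.8%.

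The table uses two-sided 5% and 90% power. Ranges cover the two variance forms and, where they apply, the 4.5 to 5.5 year pre periods.

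| Comparison | Detectable, one site (145,000) | Detectable, four sites (580,000) | Power for 7%, one site |
|---|---|---|---|
| 1 year v 1 year | 22.6% | 11.7% | 16% |
| 2 years v 2 years | 16.3% | 8.3% | 27% |
| 4.5–5.5 years v 2 years | 13.3–14.0% | 6.8–7.1% | 35–38% |
| Unlimited pre v 2 years | 11.3–11.7% | 5.8–5.9% | about 50% |

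No single-site row reaches 7%, even with a perfectly known baseline. The four-site row for the planned periods does.

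**The case against.** The strongest reply is that the two sentences describe different comparisons. The 79,000 is tied to one site against another, while the 7% is tied to change within a site, and the planned site analysis is pre versus post. On that reading the fair per-site figure is 13–14%, and setting 23% against 7% overstates the error. This stands in part: the discrepancy is about twofold on the kinder reading and about threefold on the other. It does not rescue the 7%.

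Second, both inputs are lower limits. The 145,000 is a minimum, and the 250 comes from admissions alone, whereas the outcome also draws on ambulance and emergency department records. One site could reach 7% over the planned periods if its rate were about 970 to 1,020 per 100,000, or if it were about four times larger at the stated rate. That is correct arithmetic, but the document gives neither figure, and the sentence rests its claim for every site on the 145,000.

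Third, the protocol prints no formula and does not repeat the 90% power beside the 7%. That is true. But the reproduction of 79,000 fixes the method closely, and even one-sided 5% with 80% power and an unlimited pre period leaves one site at 9.1%.

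Fourth, the eligibility minimum is justified by power for the primary effect, and the primary analysis is pooled. This also stands: on the protocol's own simple assumptions, the pooled comparison has about 90% power for 7%, so the error does not undermine the choice of site size.

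**Conclusion.** The claim of a 7% detectable reduction within each site is wrong on the protocol's own inputs. At two-sided 5% and 90% power, a site of 145,000 can detect about 13–14% pre versus post, or about 23% against another site in one year. Power for 7% in one site is 16% to 38%, depending on the comparison. About 7% is what the four sites deliver together over the planned periods, so the likeliest explanation is a pooled figure given a per-site label, although the protocol does not say so.

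The figures assume 250 attempts per 100,000 per year, 145,000 people per site, a pre period of 4.5 to 5.5 years and independent events. Repeat attempts, extra variation between years or adjustment for a trend would raise the detectable reductions. A higher linked-data rate or larger sites would lower them, but neither is stated. That 7% needs pooling over the full periods holds at 90% power; at two-sided 80% power, pooling 2 years against 2 already gives 7.2%. No per-site variant reaches 7% on the stated rate and population.

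**What to change.** Replace the sentence with one that ties each figure to its comparison, for example: assuming independent events, 250 attempts per 100,000 per year, 145,000 people per site, two-sided alpha of 0.05 and 90% power, the detectable reduction is about 7% for the four sites combined (about 5 years before, 2 years after), about 13–14% within one site before versus after, and about 23% between two sites over one year. Put in the actual pre-period lengths. If the linked-data rate and the real site populations are known, use them and show the result. It would also help to repeat the calculation for the model used in the primary analysis, since a comparison of one site with another is not the planned test.

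The cost is one paragraph. The per-site figure becomes less favourable; the sites, the data and the pooled primary analysis stay as they are.

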#### Adverse events

All serious adverse, unexpected, or possibly related events (including data breaches) will be recorded in a case report form and will be reported to the director of the LifeSpan trial and the principle investigator, [name]. A case report will be submitted to the relevant HREC agency/ies and the relevant data custodian/s. The recommendations from the HREC and data custodians will guide whether the study can continue or be stopped.

## Discussion

This study will use a stepped-wedge, cluster randomized controlled trial design to investigate the impact of the LifeSpan multilevel, multimodal intervention on rates of suicide attempt and suicide death in four geographic regions in NSW. If the program proves efficacious, the LifeSpan model can be implemented in additional high-priority regions, nationally.

This study has a number of limitations which are likely to have an impact on the stated outcomes. Firstly, the scope and intensity of some of the interventions may be difficult to implement within 2 years, particularly resource-intensive interventions (e.g., aftercare services) for which regions have not yet secured funding to establish. Achieving reductions in suicide deaths and attempts will be strongly influenced by our ability to achieve sufficient dose, reach, and sustainability in our implementation efforts. Secondly, it is also likely going to be difficult to monitor fidelity of implementation within a trial of this scale, which is problematic insomuch that the fidelity with which the strategies are implemented is likely to impact effectiveness. Thirdly, the reliance on secondary administrative data for the evaluation may be problematic, as there are data lags in coronial data as well as reporting biases in administrative data which may affect the accuracy of the primary and secondary outcomes. The fourth limitation is raised in relation to the length of the trial, only being 2.5 years’ duration, as this is unlikely to be sufficient time to embed the strategies locally to achieve population-level impact. The length of the trial also raises the risk of dropout of key staff, which may impact how the interventions are delivered on the ground. Relatedly, the interventions (e.g., school-based programs) may have a delayed effect that is not captured within the trial period. Fifth, while our analysis will account for the influence of some broader social and economic factors on suicide rates, it may not account for local changes (e.g., local changes in employment conditions, natural disasters). To address this, we are documenting significant local events and changes that may influence suicide rates and that may help to understand some regional variations in outcomes. Finally, given the complexity of the model, it will not be possible to measure the potential synergistic interactions between interventions and relate this to magnitude of change in suicide attempts at an area level or population level within the trial sites.

Some of the strengths of this study are as follows: this is the first suicide prevention trial of its kind in Australia; the emphasis on the use of evidence-based and multiple strategies to reach everyone in the community, instead of targeting a specific strategy or problem area. The results of this study are likely to have impact for research and policy, internationally, given the innovation of the LifeSpan model and the quality of the data that we will acquire. Achieving implementation at-scale and ensuring sustainability will be immensely challenging. Yet, understanding implementation and sustainability is key to the success of multilevel models such as LifeSpan, and what is learned here is likely to have implications for other highly complex problems. In addition to measuring outcomes, we have commissioned research to examine implementation and sustainability. Given the scale and complexity of this work, the comprehensive findings of this research will be published separately, and will also be referenced in discussing the main outcomes of the LifeSpan trial.

## Trial status

The selection process for trial sites was undertaken in May and June 2016, and the selection process was completed in July 2016. The trial sites were randomized and allocated in July 2016. Archival data for the evaluation will be collected from 1 April 2012, and the last data collection (indicating end of recruitment) will be acquired in August 2021 (for suicide attempt) and April 2022 for coronial data (based on current average time lags).

## Data Availability

The data that support the findings of this study are available from the National Coronial Information System, NSW Health, and NSW Ambulance, but restrictions apply to the availability of these data, which were used under license for the current study, and so are not publicly available. Data may, however, be available from the authors upon reasonable request and with permission of the above-named data custodians.

## Appendix

### The intervention components

#### Universal prevention strategies

1. *Means’ restriction.* A suicide audit report will be provided to the site-lead agencies and suicide prevention collaboratives of each site during the transition phase. This report will include the analysis of coronial, hospitalization, and ambulance data to establish the demographic, socioeconomic, and suicide means suicide risk profiles for each site. It will also provide recommendations for tailored means’ restrictions’ strategies against identified priority populations. The audit will include a detailed appendix of evidence-based strategies to reduce access to, or lethality of, means, which is intended as a practical strategy to help sites decide what specific means’ restriction strategies should be implemented in their local region
2. *Media guidelines.* Local media representatives will receive group-based face-to-face media training delivered by Mindframe Australia, aimed at reducing dangerous reporting of suicide, and increasing responsible and respectful coverage of mental health and suicide in the media. The target audience is local journalists, suicide prevention multiagency group members, organizational leaders, and local leaders who might be asked to comment on suicide by media and who are involved in community support after suicide. The training will be a 2-day, face-to-face group program delivered in Year 1 of active implementation at each site, with a half-day refresher program delivered in Year 2
3. *School-based suicide prevention.* Year-9 high-school students in all public, independent, and Catholic high schools within the four sites will be offered an evidence-based, universal suicide prevention program designed to reduce stigma, increase help-seeking behaviors and resilience, and reduce suicidal ideation and behaviors. The Youth Aware of Mental Health (YAM) program will be delivered over the 2-year duration of the LifeSpan trial, meaning two consecutive cohorts of Year-9 students will receive YAM. The YAM program was developed by researchers and clinicians from the Karolinska Institute in Sweden and Cornell University in the USA. Its primary aim is to raise awareness about suicide risk and the factors that may protect against suicidality. YAM consists of five sessions delivered over a 3-week period, and involve a mix of direct instruction, reading material, visual information and interactive workshops where young people are encouraged to role-play skills within a supervised environment
4. *Public awareness.* Centrally developed resources and materials with key messaging will be disseminated to the general public within each of the sites through a series of awareness-raising community events, in partnership with “R U OK” campaign providers. The LifeSpan resources and messages will be designed to engage the community in suicide prevention, with a call to action; for example, to complete gatekeeper training; sign up to be a YAM helper; to reduce stigma; and to increase identification and referral of individuals with suicidal ideation or self-harming behaviors. Major awareness-raising events will be held in September in Year 1 and Year 2, during the national suicide prevention awareness week

#### Selective strategies

5. *Gatekeeper training.* Question, Persuade, Refer (QPR) training will be provided to all community members in each of the four sites, to skill them in being able to recognize and respond positively to someone exhibiting suicide warning signs and behaviors, including providing appropriate referral information. This will be a brief (60-min) training program, that individuals will sign up to, and then they will be able to access their licence for up to 3 years, to refresh their gatekeeper skills. The digital QPR program will be available at all times throughout the active implementation period in each site, and it will be advertised through the public awareness strategy to increase uptake in the community
6. *Frontline responder training.* First responders (police, paramedics, and ED staff) will receive face-to-face and online training to support individuals with suicidal ideation or self-harming behaviors. Training will be provided to first responders in each of the four sites. Where training already exists, such as the NSW Police Mental Health Intervention Training (MHIT) program, support will be offered to ensure that the program is meeting local needs. The local implementation teams will identify key decision-makers within each sector to work with them in implementing training. The total number of staff trained will vary by sector and site
7. *Psychosocial treatments.* A guide to evidence-based psychological and pharmacological treatments for the care of individuals with suicidal ideation and/or behaviors will be provided to privately and publicly employed psychologists, psychiatrists, and other mental health professionals at each site. The Advanced Suicide Prevention Training program, designed and facilitated by the Black Dog Institute, will be provided for these professionals, to inform appropriate assessment of suicidal ideation and/or behaviors. This 6-h face-to-face group program trains participants to undertake a suicide risk assessment effectively; develop a collaborative safety plan; implement a team approach to treatment planning; provide effective management following a suicide attempt; and respond to the needs of people bereaved by suicide. This training will be supplemented by information on local referral pathways, delivered by a local subject-matter expert and program champion. We aim to train 200 mental health professionals at each of the four sites. The Collaborative Assessment and Management of Suicidality (CAMS) framework will be implemented in relevant healthcare settings in each site, with mental health teams selected to participate according to their role in providing treatment to people at risk of suicide. CAMS is an evidence-based approach to managing suicide risk [17, 18] and its implementation entails structured training and implementation support

8. *General practitioner (GP) capacity building and training.* General practitioners will receive training and practice support to identify and refer individuals with suicidal ideation or self-harming behaviors. The Advanced Suicide Prevention Training program, designed and facilitated by the Black Dog Institute, will be provided to general practitioners. This 6-h face-to-face group-based program trains participants to undertake a suicide risk assessment effectively; develop a collaborative safety plan; implement a team approach to treatment planning; provide effective management following a suicide attempt; and respond to the needs of people bereaved by suicide. In addition, general practices will be provided with training by the Black Dog Institute-developed “StepCare” program. StepCare is designed to digitally screen patients for depression, anxiety, substance use, and suicidal thoughts while they wait for their appointment. GPs will be provided with detailed immediate feedback, verbal scripts and recommendations for the patient via the practice management software. Training for the general practice staff in StepCare will come from a trainer located within the Primary Health Network, who will have received “train-the-trainer” from the Black Dog Institute StepCare coordinator. We aim to train and/or provide StepCare access to 50–60 general practitioners per site

